# Metacognitive therapy vs. eye movement desensitization and reprocessing for posttraumatic stress disorder: study protocol for a randomized superiority trial

**DOI:** 10.1186/s13063-017-2404-7

**Published:** 2018-01-08

**Keywords:** Posttraumatic stress disorder, Randomized controlled trial, EMDR, Metacognitive therapy

## Abstract

**Background:**

The psychological treatment of choice for patients with severe posttraumatic stress disorder (PTSD) is cognitive behavioural exposure therapy or Eye Movement Desensitisation Reprocessing (EMDR). Whilst these are the most effective treatments, approximately 30–45% of the patients show no significant improvements and follow-up data are sparse. Furthermore, a proportion of patients with severe trauma does not benefit or avoid exposure therapy due to the potential to overwhelm them. Therefore, it is necessary to search for effective methods that do not require exposure. Metacognitive therapy (MCT), a recent treatment approach to PTSD that does not require exposure, has potential strong treatment effects but so far a comparison with EMDR has not been made.

**Methods/design:**

This study is a two-arm, parallel, randomized, superiority trial comparing the effectiveness of MCT with EMDR. One hundred patients with a primary diagnosis of chronic PTSD will be included and will receive 12 sessions of one of the treatments. The primary outcome is severity of PTSD symptoms assessed with the Posttraumatic Diagnostic Scale (PDS) measured post-treatment (3 months). Secondary outcomes include symptom severity (PDS) and measures of anxiety, depression, metacognitive beliefs at 3-month and 12-month follow up.

**Discussion:**

This randomized study is the first to compare MCT with EMDR with 12-month follow-up. The study will indicate the comparative effectiveness of MCT against EMDR and the stability of effects when delivered in an outpatient clinical setting.

**Trial registration:**

ClinicalTrials.gov, NCT01955590. Registered on 24 September 2013.

**Electronic supplementary material:**

The online version of this article (doi:10.1186/s13063-017-2404-7) contains supplementary material, which is available to authorized users.

## Background

Posttraumatic stress disorder (PTSD) is a frequently occurring and often debilitating anxiety disorder resulting from exposure to trauma [1, 2]. Prolonged exposure therapy [3], trauma-focused cognitive behavioural therapy (CBT) [4] and eye movement desensitisation reprocessing (EMDR) [3] are recommended treatments for PTSD. Each of these approaches utilises exposure to trauma memories as one of the main components in the intervention. The efficacy of these treatments is supported by a large number of studies that show equivalent levels of outcome with no particular treatment evidencing superiority [4, 5]. However, it has been noted that EMDR has to some degree been compared to other active treatments for PTSD in rigorous controlled trials.

Although the majority of patients improve, a substantial proportion of patients drop out of treatment [4, 6, 7], present with residual symptoms following treatment or fail to improve [7–9]. Approximately 37–51% of patients completing therapy improve significantly [8], which leaves substantial room for improving outcomes. Furthermore, a substantial portion of the clinical trials on PTSD have major methodological limitations [10].

EMDR is based on the assumption that posttraumatic symptoms are caused by traumatic experience(s) being stored in an unprocessed way disconnected from existing memory networks [11]. In EMDR the patient is asked to focus on trauma-related imagery, negative cognitions and body sensations while simultaneously focusing their attention on a bilateral physical stimulation. The procedure in EMDR is postulated to facilitate the processing of the traumatic memory into existing memory networks [11]. A number of theories explaining the potential mechanisms underlying the effects EMDR have been proposed (e.g. [12]). The importance of bilateral eye movements is often highlighted, but there is still substantial controversy about whether bilateral eye movements are of importance [13] or not [14–16]. It is also important to note that dismantling randomized controlled trials comparing EMDR with and without bilateral eye movements does not in itself provide sufficient evidence on potential mediators and mechanisms for treatment outcome [17]. To the best of your knowledge, to date no RCTs have been conducted in EMDR that incorporate the investigation of potential mediators of treatment outcome as outlined by Kazdin [17, 18]. As such there is still a pressing need for trials investigating potential mediators of treatment outcome of trauma-focused treatments generally and EMDR specifically [19]. EMDR is usually considered an evidence-based treatment for PTSD [5, 8, 20].

Metacognitive therapy (MCT) [21, 22] is one of the more recent approaches in the treatment of PTSD. The focus of MCT is on removing specific barriers to spontaneous recovery that is purported to normally occur following trauma. Metacognitive beliefs are beliefs and theories people have about their thinking and how to regulate their thoughts. It could be beliefs that thoughts have a special meaning (sinful thoughts) or that thoughts may be harmful or uncontrollable. The metacognitive beliefs are hypothesised to underlie an unhelpful response style consisting of worry, rumination and threat monitoring, and other coping behaviours such as attempting to fill gaps in memory. These response styles prevent cognition and arousal returning back to basal levels of processing a threat-free environment. In effect PTSD symptoms are maintained because these factors prolong threat-related processing and interfere with the downregulation of subcortical arousal. In contrast to EMDR, MCT does not involve prescribed exposure exercises or restructuring of negative trauma-related memories.

MCT has been shown in early trials to be an effective, time-limited (8–10 sessions), well-tolerated and apparently highly effective treatment option for both recent onset and chronic PTSD [23–26]. The core treatment has been investigated using an A-B direct replication series [23], an open trial [24] and a randomized controlled trial with delayed treatment as a control condition [25]. These preliminary results indicate that MCT is a well-tolerated treatment and that most patients experience significant improvements that are maintained at follow up. Furthermore, a clinical trial to compare MCT with prolonged exposure (PE) has shown that MCT performs better [26]. This trial demonstrated a statistically significant reduction in reported PTSD symptomatology, depression and anxiety symptoms post-treatment in the MCT group compared to the PE condition. In conclusion, MCT appears to be a highly promising treatment for PTSD, generating large clinically significant treatment effects for clients exposed to a range of traumatic experiences, which include accident survivors and assault and rape victims. However, to date no study has directly compared MCT with EMDR. The aim of the present study was to undertake such a comparison to determine the relative effectiveness for each of the treatments immediately following treatment and at 12-month follow-up.

The following aims and hypotheses were set up in the trial: (1) to evaluate the effectiveness of MCT compared with EMDR in PTSD using a comparative randomized controlled study; (2) to examine potential moderators and mediators of treatment outcome; (3) to examine and compare the relapse rate in MCT and EMDR.

The main hypotheses to be tested include the following:Both treatments will be effective and demonstrate significant improvements in symptom severity indicated by decreased scores for trauma symptoms, anxiety level and depressive symptomsPrevious findings on effect sizes [27] indicate that MCT will demonstrate higher recovery rates than EMDR based on the symptom criteria of the Posttraumatic Diagnostic Scale (PDS).

## Methods

### Study design

The study is a two-arm randomized controlled superiority trial with a pre-post and 12-month follow up comparing the effectiveness of MCT and EMDR in the treatment of PTSD. The primary hypothesis is that MCT will be superior to EMDR in reducing PTSD symptoms measured with the PDS post-treatment. The secondary hypothesis is that superiority of MCT will be maintained at 12-month follow up. Stratified randomization where equal numbers of participants are allocated to each condition according to chronicity of PTSD, presence and severity of borderline personality traits (four criteria fulfilled) and gender will be used. The independent variable is a manualised MCT condition (12 sessions) or manualised EMDR (12 sessions). The other secondary outcome measures are the Impact of Events Scale-revised (IES-R), posttraumatic symptoms assessed using the Posttraumatic Stress Scale-Interview (PSS-I), depression assessed using the Beck Depressions Inventory (BDI)-II, anxiety levels assessed using the Beck Anxiety Inventory (BAI)-II, and metacognitions assessed using the Metacognitive Questionnaire (MCQ)-30). The present protocol has been prepared in accordance with relevant items from the SPIRIT Checklist (see Additional file 1) and the SPIRIT Figure (Fig. 1).

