### Participants

Eligible patients who meet *Diagnostic and Statistical Manual of Mental Disorders-Fourth Edition* (DSM-IV) criteria for PTSD and are aged between 16 and 70 years of age and consent to participation will be included. Diagnosis will be determined with the Anxiety Disorders Interview Schedule (ADIS-IV). Patients must not have previously received EMDR or MCT. Patients with psychotic symptoms, severe depression, alcohol or drug abuse, acute suicidality, borderline personality disorder or symptoms of PTSD for less than 6 months will be excluded.

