### Randomization

Participants meeting the inclusion criteria are randomized to either EMDR or MCT. Randomization is stratified on gender and borderline personality disorder characteristics, as both gender and BPD characteristics have been found/are assumed to impact treatment outcome. Before initiating the trial the principal investigator ([name]) generated a random-number table using SPSS. Due to the use of a printed random-number table the allocation is not absolutely/perfectly concealed. Authors [name] and [name] assign allegeable participants to the conditions based on the pre-defined random-number table.

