### Data analysis plan

All data will be analysed based on an intention-to-treat (ITT) approach with all randomized patients entering the analysis. Missing data will be estimated by SPSS multiple imputation on the primary measure to estimate the scores of those with missing data. The number of imputations will depend on the amount of missing data. The primary outcome is a continuous longitudinal measure (PDS), therefore linear mixed-model analysis (LMM) will be run. Random effects will be applied to the patient-specific intercepts and covariates will be included in all analyses based on imbalance between trial arms. The effects of the treatments will be examined using the interaction effect of group × time from the mixed-effects analysis with PDS post-treatment as the primary outcome.

In addition to the primary analyses we will conduct exploratory moderation and mediation analyses. Moderation analyses will be conducted with both individual and combined moderators [48, 49]. Mediation analyses [50, 51] will be conducted with PDS as the outcome and PTCI, MCQ-30 and SRS as potential mediators.

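### Study design names three stratification factors and Randomization names two, so it is unclear whether chronicity was controlled by design; choosing covariates by observed imbalance does not repair this

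*Protocol article*

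**What the plan says.** The protocol article describes the allocation twice.

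- **Study design:** stratified randomisation "according to chronicity of PTSD, presence and severity of borderline personality traits (four criteria fulfilled) and gender will be used". That is three factors, with a threshold given for borderline traits and none for chronicity.
- **Randomization:** "Randomization is stratified on gender and borderline personality disorder characteristics", with the reason given "as both gender and BPD characteristics have been found/are assumed to impact treatment outcome". That is two factors. The same section says that the principal investigator "generated a random-number table using SPSS" before the trial began.

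Two other sections bear on the point. Under Participants, the exclusions end with "borderline personality disorder or symptoms of PTSD for less than 6 months will be excluded"; this sets an eligibility floor for chronicity, not a cut-off between strata. The Data analysis plan names no stratification factor and says that "covariates will be included in all analyses based on imbalance between trial arms". The primary test there is the group × time interaction from a linear mixed model with patient-specific random intercepts.

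**The concern.** Factors used to stratify the randomisation should be known and carried into the primary analysis. Here a reader cannot tell whether chronicity was balanced by the allocation or left to chance. If it was not in the table, Study design claims a control that the trial did not have. If it was, Randomization misdescribes the design, and the analysis should include it.

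The covariate rule adds to the problem. A factor that stratification has balanced will rarely show an imbalance, so a rule driven by imbalance tends to exclude the factors the design used. It also means that the adjustment set is chosen after the data are seen. If chronicity enters the model later, nobody can tell from the article whether it entered because of the design or because of the data.

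**Working it through.** **Comparing the sections**

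| Item | Study design | Randomization | Data analysis plan |
|---|---|---|---|
| Gender | listed | listed | not named |
| Borderline traits | listed, four criteria | listed, no threshold | not named |
| Chronicity | listed, no cut-off | not listed | not named |

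The Randomization list cannot be read as a shortened form of the other. Its reason refers to both factors, which closes the list at two. Neither section is marked as superseded, and the table was fixed before the trial, so the two descriptions cannot both be right.

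**The plan's own figure.** The sample size section gives means of 10.4 and 18.3 (difference 7.9), SD 10.6, 80% power and two-sided 5%. Then n per arm = 2 × (1.96 + 0.84)² × (10.6/7.9)² ≈ 28.3, rounded up to 29, or 58 in total. The stated figure reproduces. It uses no stratification factor, so the contradiction does not touch it.

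**Number of strata.** Assume binary factors; the article does not state the levels. With the planned 100 patients, two factors give 2² = 4 strata of 25 on average, and three give 2³ = 8 strata of 12.5.

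**Cost of omitting balanced strata.** Let R² be the share of the variance of the analysed contrast that the strata explain. The documents give no value; 10–20% is an assumption. With balance within strata, the model that omits them overstates the standard error by 1/√(1 − R²), and the nominal critical value of 1.96 acts as 1.96/√(1 − R²).

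| R² | SE ratio | Effective critical value | True two-sided type I error |
|---|---|---|---|
| 0.10 | 1/√0.90 = 1.054 | 2.07 | 3.9% |
| 0.20 | 1/√0.80 = 1.118 | 2.19 | 2.8% |

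A wider assumed range of 5–30% gives 4.4% to 1.9%. The error is on the conservative side, so what is lost is power. For a single post-treatment comparison at 29 per arm, the standardised difference is 7.9/(10.6 × √(2/29)) = 2.84. Power without the strata is Φ((2.84 − 1.96)/√(1 − R²)), or 82.3% and 83.7% at R² of 0.10 and 0.20. With them it is Φ(2.84/√(1 − R²) − 1.96), or 84.9% and 88.7%.

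**Which R² matters.** The planned test is group × time. With complete data, that estimate rests on within-patient change from baseline to post-treatment. A factor that adds the same amount to PDS at both times cancels from the change score, so its R² for this contrast is about zero and its omission costs almost nothing. The figures above apply only to the part of a factor's effect that acts on change. For the same reason, adding the factor as a main effect leaves the group × time estimate and its standard error essentially unchanged; only a factor × time term can explain variance in change.

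**The case against.** The strongest reply is that this is one wording slip about one factor. Two of the three factors agree, the eligibility floor of six months already narrows the range of chronicity, neither the primary outcome nor the sample size changes, and a full covariate list is commonly left to an analysis plan that is not shown. Most of that stands, and it limits the size of the point. It does not remove the contradiction. No analysis plan can make two incompatible accounts of a table already generated both true, and the covariate rule is stated in the article, not left open.

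Several stronger readings are tempting, and the documents do not support them.

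- *The strata are undefined.* They are ambiguous. Gender and borderline traits appear in both lists, and Study design gives a borderline threshold.
- *The table was unrestricted, so equal numbers per condition could not be delivered.* Equal numbers are mentioned only in Study design. Randomization says that allocation is stratified and is silent on how the list was laid out. An article commonly leaves block structure to the full protocol, so nothing can be concluded from the silence, and it gives no ground for a change of allocation method. Such a change would also come very late, since Trial status expects treatment to end by the close of 2017.
- *Chance imbalance in chronicity would go uncorrected.* The planned rule would respond to an observed imbalance. The weakness is that it does so after the fact.
- *The type I error is wrong by a known amount.* The figures rest on an assumed R² and on effects that act on change. Where they apply, the test is conservative.

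**Conclusion.** The point holds as a contradiction that should be resolved before analysis. Three factors in one section and two in another cannot both describe the table, and the factor in dispute is chronicity. The rule for choosing covariates compounds it, because it tends to omit whichever factors were balanced.

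The statistical effect is modest and conditional. It ranges from close to nil, for a factor with the same effect on PDS before and after treatment, to a standard error about 5–12% too wide and a type I error of about 3.9–2.8%, if balanced strata explain 10–20% of the variance of the analysed contrast. That range is an assumption. A reader might infer that the primary model cannot be matched to the design, or that false positives are inflated. The first is not shown, because the allocation table exists and can be checked; the second is the wrong direction when strata are balanced.

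**What to change.** 1. Check the allocation table generated before the trial and correct whichever section is wrong.
2. State the factors actually used, with their levels and cut-offs: the borderline threshold and, if it was used, the chronicity cut-off.
3. In the Data analysis plan, replace selection by imbalance with those factors, prespecified in the primary mixed model, each as a main effect and a factor × time term.
4. If chronicity was not a stratification factor, delete that claim from Study design. If adjustment for it is still wanted, prespecify it as a covariate in the same way.

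The cost is one check of an existing list, a wording correction and a few extra model terms. No change to sample size or allocation is needed. The article reports recruitment as ongoing, so the correction can be dated before the outcome data are analysed.

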**Fig. 1 Fig1:**
[figure not shown]
Schedule of enrolment, interventions, and assessments. *Abbreviations*: *ADIS-IV* Anxiety and Depression Interview Scale-IV; *BDI* Beck Depression Inventory; *BAI* Beck Anxiety Inventory; *IES-R* Impact of Event Scale- revised; *IIP-64* Inventory of Interpersonal Problems-64; *PDS* Posttraumatic Diagnostic Scale; *MCQ-30* Metacognitive Questionnaire-30; *PSS-I* Posttraumatic Stress Disorder Scale-Interview; *PTCI* Post Traumatic Cognitions Inventory; *SRS* Session Rating Scale

### Participants

Eligible patients who meet *Diagnostic and Statistical Manual of Mental Disorders-Fourth Edition* (DSM-IV) criteria for PTSD and are aged between 16 and 70 years of age and consent to participation will be included. Diagnosis will be determined with the Anxiety Disorders Interview Schedule (ADIS-IV). Patients must not have previously received EMDR or MCT. Patients with psychotic symptoms, severe depression, alcohol or drug abuse, acute suicidality, borderline personality disorder or symptoms of PTSD for less than 6 months will be excluded.

### Measures

Both clinical assessments and self-report measures will be used in this study. Figure 1 shows the time distribution of each rating or measure (see Fig. 1).

#### Posttraumatic Diagnostic Scale *(PDS)*

The PDS [28] is a self-report diagnostic and symptom severity measure of PTSD based on the DSM-IV criteria. It consists of a total of 49 items. Of these, 17 items are related to diagnostic criteria as defined by the DSM-IV and these are rated on a 4-point Likert scale. The symptom severity score (PDS-SSS) was used to indicate severity of symptoms. Test-retest reliability over 3 weeks for the diagnosis of PTSD was acceptable (k = 0.74) and the validity is confirmed by high overlap between PDS and the structured clinical interview for PTSD (82%) [28].

#### Anxiety Disorders Interview Schedule *(ADIS)*

The ADS [29] will be used as the diagnostic measure. This is a structured clinical interview based on the DSM-IV criteria.

#### PTSD Symptom Scale – Interview *(PSS-I)*

The PSS-I [30] was designed as a flexible semi-structured interview about DSM-IV PTSD symptoms to make a diagnosis of PTSD and obtain an estimate of the severity of the symptoms. PTSD severity is determined by the sum score of the 17 PSS-I item ratings. Scores range from 0 to 51. PTSD diagnosis is determined by counting the number of symptoms endorsed (a rating of 1 or greater) per symptom cluster: 1, re-experiencing; 3, avoidance; and 2, arousal symptoms are needed to meet diagnostic criteria. The PSS-I has been compared to the Clinician-Administered PTSD scale (CAPS) and they correlated strongly with each other and with the Structured Clinical Interview for DSM Disorders (SCID) [31]. These results indicate that PSS-I can be used in the same way as CAPS in the assessment of PTSD.

#### Beck Anxiety Inventory (*BAI)*

The BAI [32] is an inventory designed to assess the broad spectrum of anxiety symptoms and consists of 21 items. The respondents score the degree to which they have been impaired by the symptoms during the last week. Total scores range from 0 to 63, and a higher score indicates greater levels of anxiety. The BAI has high internal consistency and test-retest reliability.

#### Beck Depression Inventory *(BDI- II)*

The BDI-II [33] will be used as a measure of depressive symptom severity. The BDI-II ranges from 0 to 63 and has an alpha of 0.94, and test-retest reliability of 0.93.

#### Impact of Event Scale – revised *(IES-R)*

The IES-R [34] is one of the most commonly used measures of PTSD symptoms [35]. The respondents rate the frequency of the subjective experience of distress in relation to their traumatic event within the last week. It consists of two subscales for intrusion and avoidance. The psychometric properties are well-validated [35, 36].

